#### The Newfoundland and Labrador Bariatric Surgery Cohort (BaSCo) study

##### Study objective

The objective of the current study is to examine short- to mid-term outcomes (2–4 years) associated with LSG. Eligible patients who have undergone LSG will be followed during and after surgery to assess health and other outcomes. Specific study objectives are to examine:30-day complication rate and mortality, and long-term complications (e.g., gastroesophageal reflux, micronutrient deficiencies).reduction in weight and/or body mass index (BMI), including predictors of successful weight loss.improvement or resolution of co‐morbid conditions (i.e. diabetes, hypertension, dyslipidemia, NAFLD, PCOS).changes in prescription and over-the-counter medication use.improvement in measures of health‐related quality of life andthe economic consequences associated with LSG (e.g., direct costs and indirect costs).

In the short- to mid-term we hypothesize a low rate of complications, a marked reduction in weight, improvement/resolution of comorbid conditions, a reduction in obesity-related medications, an improvement in quality of life, and a decrease in direct healthcare and indirect costs compared to pre-surgery costs.

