4. Physician Fees (self-report)	# of encounters Provider specialty Service provided	Patient interview (standardized case report form)	Estimated using MCP Physician Claims	Information obtained every 6 months
5. Medications	Name dosage, frequency & duration	Patient interview (standardized case report form)	NL Drug (Provincial Formulary)	Information obtained every 6 months
6. Transfer Payments	Unemployment insurance Disability benefits	Patient interview (standardized case report form)	Patient Reported	Information obtained every 6 months
8. Employment status, absenteeism	Employment status in past year (# hours/week, # weeks) Absenteeism in past year (# days) Annual income (by quintile)	Patient interview (standardized case report form)	Average wage rate by age, sex and region from Statistics Canada	Information obtained every 6 months
9. Weight Loss Interventions	Weight loss program, meal replacements, physical trainer, exercise programs, alternative therapies (Binary Y/N)	Patient interview (standardized case report form)	Patient reported out of pocket cost Costs lists of rehabilitation supplies & equipment	Information obtained every 6 months
10. Mobility and Medical	Mobility aids, home modification/renovations, rehabilitation, paid personal assistance (household activities and home productivity, driving) (Binary Y/N)	Patient interview (standardized case report form)	Patient reported out of pocket cost/co-payments for medical services Costs lists of rehabilitation supplies & equipment	Information obtained every 6 months

*DAD* Discharge Abstract Database, *LOS* Length of stay, *CIHI* Canadian Institute for Health Information, *CDMS* Clinical Database Management System, *RIW* Resource Intensity Weight, *MCP* Newfoundland and Labrador Medical Care Plan, *EH* Eastern Health

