#### Secondary outcomes

Complications of surgery30-day complication rate and mortality will be reported. Longer-term complications such as gastroesophageal reflux and micronutrient deficiencies will be examined. To examine micronutrient deficiencies, the following biochemical parameters associated with micronutrients will be assessed (25-hydroxyvitamin D (25-OH-D), parathyroid hormone (PTH), calcium, vitamin B12, ferritin, mean cell volume (MCV) and hemoglobin). The analysis for 25-OH-D used liquid chromatography coupled with tandem mass spectrometry. Hemoglobin and MCV were analyzed on the Beckman Coulter®HMX Hematology Analyzer, while ferritin, vitamin B12, and intact PTH were analyzed on the Architect i System by Abbots Diagnostics. Calcium was analyzed on the Architect c System by Abbots Diagnostics.Comorbid Condition Improvement/ResolutionImprovement in comorbid conditions (i.e. hypertension and dyslipidemia) is defined as any reduction in medication use or treatment. Comorbidity resolution is defined as complete cessation of treatment/medication.For the comorbid conditions of prediabetes and type 2 diabetes mellitus, specific definitions of diagnosis are used as outlined in the Canadian Diabetes Association Clinical Practice Guidelines [66]. Prediabetes is defined as fasting plasma glucose (FPG) levels of 6.1–6.9 mmol/L and/or glycated hemoglobin (A1C) levels of 6.0–6.4 % [66]. Type 2 diabetes mellitus is defined as FPG ≥ 7.0 mmol/L and/or A1C ≥ 6.5 % [66].Additional criteria will used to assess improvement and resolution of prediabetes and diabetes [67]. Case definitions of improvement and remission of prediabetes will be as follows: *Improvement* will be based on achievement of the following: (1) lower glycemic measures (2) at least 1 year’s duration, and (3) pharmacologic therapy required but at a lower dose. *Normalization* is defined as (1) normal glycemic measures (2) at least 1 year’s duration, and (3) pharmacologic therapy required but at a lower dose. *Remission* is based on (1) normal glycemic measures (2) at least 1 year’s duration, and (3) no active pharmacologic therapy. Case definitions of improvement and remission of Type 2 diabetes mellitus [67] will be defined as follows. *Improvement* will be based (1) hyperglycemia below diagnostic thresholds for T2DM (2) at least 1 year’s duration, and (3) pharmacologic therapy required but at a lower dose. *Partial remission* is based on the following (1) hyperglycemia below diagnostic thresholds for T2DM (2) at least 1 year’s duration, and (3) no active pharmacologic therapy. *Complete remission* is based on the following criteria (1) normal glycemic measures (2) at least 1 year’s duration, and (3) no active pharmacologic therapy.The status of specific biochemical parameters associated with NAFLD prior to and following LSG will be assessed using the following markers: total bilirubin, alanine phosphatase (ALP), alanine transaminase (ALT), gamma glutamyl transpeptidase (GGT), high-density lipoprotein (HDL), low-density lipoprotein (LDL), and triglycerides. Biochemical parameters associated with NAFLD were analyzed on the Architect c System by Abbots Diagnostics.The prevalence of PCOS will be determined prior to surgery based on self-report while changes in related (e.g., period frequency and regularity, menstrual flow and intensity, hirsutism, acne, fertility, post-surgery conception) and metabolic symptoms (insulin sensitivity, T2DM, dyslipidemia, hypertension) will be examined 1-year after LSG.Change in medication useChanges in prescription and over-the-counter medication use and associated costs will be examined including total number of medications and changes (dose changes, medication discontinuations, and initiation of additional medications) by disease indication.Quality of LifeHealth related quality of life is assessed using validated instruments. Generic and disease-specific instruments will be used. All participants will complete the Short Form (SF)-12, Euroqol (EQ)-5D, and the Impact of Weight on Quality of Life (IWQOL)-Lite pre-surgery at 6, 12, 18, and 24 months after surgery. The SF-12 (Version 2) is a condensed 12-question version of the SF-36 [68]. It yields a physical and a mental health component summary score. Three-to-five point difference in either score are considered clinically meaningful [69, 70]. The EQ-5D is an indirect preference-based health survey that consists of a 5 dimension descriptive system [71] and an overall health visual analog scale (EQ- VAS). A 0.03 point difference in EQ-5D index score and 10 point difference on the EQ-VAS are considered clinically meaningful [72]. The IWQOL-Lite is a short form of the IWQOL and is the first instrument specifically developed to assess the effects of obesity on the quality of life of persons who are seeking weight loss treatment [73]. The IWQOL-lite consists of 31 items that describe 5 domains of obesity-specific HRQL. A difference in the total score of 7–12 points for IWQOL-Lite is considered clinically meaningful [74].Economic consequences of bariatric surgeryDirect healthcare use/costs (e.g., hospitalizations, physician visits, medication use) and indirect costs (e.g., cost of weight loss interventions, employment and absenteeism, home productivity, transfer payments) will be compared 3 years prior to surgery and 2 years post- surgery in order to determine the economic consequences of bariatric surgery.

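### Indirect costs are defined to include both wage-valued lost work and the benefits paid for not working; if combined, the overlapping part is counted twice

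*Protocol article*

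**What the plan says.** The economic part of Secondary outcomes names the components of the outcome: "indirect costs (e.g., cost of weight loss interventions, employment and absenteeism, home productivity, transfer payments"). Together with direct costs, these "will be compared 3 years prior to surgery and 2 years post- surgery in order to determine the economic consequences of bariatric surgery".

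Table 2, under Evaluation of health care utilization and costs, treats two of these components as cost categories in their own right:

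- "6. Transfer Payments" covers "Unemployment insurance Disability benefits", with patient report as the costing source.
- Row 8 collects "Employment status in past year (# hours/week, # weeks") and "Absenteeism in past year (# days"), with the costing source "Average wage rate by age, sex and region from Statistics Canada".

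The Study objective section hypothesises "a decrease in direct healthcare and indirect costs compared to pre-surgery costs", so indirect costs are judged as a group. The Abstract says the same in similar terms. The Data analysis section adds a cost-effectiveness analysis. The article names no costing perspective, and it does not say that benefits are netted against lost wages or kept out of the indirect-cost figure.

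**The concern.** Unemployment and disability benefits are paid because a person is not working. Row 8 supplies a wage with which to value that same time. When both are components of one cost heading, a period out of work can be charged once as lost wages and again as the benefit that partly replaces them.

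The economic consequences are one of six stated objectives, and the article says its findings are meant to inform health policy. If patients move from benefit to work after surgery, a combined indirect cost credits them with both the wages gained and the benefit stopped. If patients stop work, it charges them twice. Either way, the reported change in indirect cost would not measure one well-defined quantity.

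**Working it through.** The article states no cost amount, wage or benefit rate, so there is no figure to reproduce. The check has two parts.

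**1. Does any perspective count both items in full?**

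| Perspective | Wage-valued lost work | Unemployment and disability benefits |
|---|---|---|
| Society | Cost (lost production) | Redistribution, not resource use: leave out |
| Government payer | The patient's full wage is not its cost: leave out | Cost |
| Patient | Cost (lost income) | Income that offsets the loss: subtract |

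No row adds both. Whichever perspective is chosen, the list of components in Secondary outcomes has to change.

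**2. How large could the overlap be?**

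Inputs, all assumed and on a common per-year basis:

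- L = lost work valued at the wage, set to 100 before surgery and 80 after.
- r = benefit as a share of the wage, 0.3 to 0.8.
- s = share of that lost work covered by a benefit, 0.25 to 1.

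Lost work alone costs L. Lost work plus transfers costs L + L×r×s = L(1 + r×s), so the overstatement is r×s. The change from 100 to 80 is a saving of 20 when transfers are left out. With transfers added:

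| r | s | r×s | Before | After | Apparent saving |
|---|---|---|---|---|---|
| 0.3 | 0.25 | 7.5% | 107.5 | 86.0 | 21.5 |
| 0.55 | 0.5 | 27.5% | 127.5 | 102.0 | 25.5 |
| 0.8 | 1 | 80% | 180.0 | 144.0 | 36.0 |

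If lost work rises from 80 to 100 instead, the true increase of 20 appears as 21.5, 25.5 or 36.

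A change can also appear where lost work does not change. Hold L at 100 and r at 0.55, and let coverage fall from s = 0.5 to s = 0.25. The combined cost goes from 100 × (1 + 0.275) = 127.5 to 100 × (1 + 0.1375) = 113.75. The apparent saving is 13.75, although the same amount of work is lost.

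**The case against.** The strongest reply is that the article never writes the sum. Secondary outcomes gives an open list of examples, and Table 2 is a list of categories and sources with no total row. A comparison category by category would fit the text, and transfers already have their own row. Perspective and aggregation rules are also commonly left to a fuller document that is not shown here.

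Part of this stands. A reader might infer that the plan explicitly adds row 6 to row 8, but it does not; the double count follows only if the components are combined. The hypothesis about indirect costs as a group makes that the natural use, though not a stated one. Leaving the perspective to a fuller document does not rescue the definition, because no perspective supports the list as written.

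Three further limits also stand:

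- **Overlap is partial.** Row 8 names a wage source but does not say whether non-employment is priced, or against what reference hours. If the wage is applied mainly to days absent from a job, few of those days may carry a benefit and s is small.
- **A tempting figure is too strong.** A reader might assume that benefits replace 40–60% of the wage and conclude that each change is inflated 1.4 to 1.6 times. This is 1 + r with s = 1, the case where a benefit covers all the lost time. The documents support neither the rate nor full coverage.
- **Direction is conditional.** A reader might infer a bias towards the study's hypothesis. This follows only if net employment rises or benefit uptake falls after surgery, and the documents do not show that either happens.

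**Conclusion.** The point holds as a flaw in the definition of the indirect-cost outcome. The article places wage-costed employment and absenteeism and income-replacement benefits under one cost heading. If they are combined as the definition implies, the overlapping part is counted twice. That would be wrong from a societal, a government or a patient perspective.

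The size cannot be derived from the documents. Under the assumed ranges the overstatement of indirect cost is 7.5% to 80%, and lower still if little of the valued time attracts a benefit. With r and s constant over time, the same percentage applies to the pre/post change; if uptake changes, part of the change may be spurious. The saving is exaggerated if patients move from benefit to work, and the opposite transition exaggerates a loss. If the items are only tabulated separately and never combined, the arithmetic harm disappears, but transfers are still misclassified as a component of indirect cost.

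This affects one component of a secondary objective. It should be corrected before the cost comparison is made, and it has no bearing on the weight-loss outcome.

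**What to change.** In Secondary outcomes and in Table 2:

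- Take transfer payments out of the indirect-cost total.
- For a societal total, value lost work at the wage rate from row 8, and state that this is the perspective.
- Report unemployment insurance and disability benefits in a separate public-payer table that excludes lost wages.

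The data are already collected in the patient interviews, so the change is one of wording plus a small amount of extra tabulation. The reported saving may be smaller than it would have been with the items combined.

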#### Patient selection criteria for bariatric surgery

The eligible population consists of all patients who (1) meet the Canadian Practice Guidelines criteria for the surgical treatment of obesity (BMI ≥35 with risk factors, or BMI ≥ 40) [3], (2) are referred by their primary care provider to the bariatric team using a standardized referral form submitted to a central intake system, and (3) receive preliminary eligibility screening by the nurse practitioner. Following mandatory attendance at a pre-surgical bariatric surgery general orientation and an education session provided either face-to-face or via webinar, patients are required to undergo an extensive pre-operative work-up which includes a 2-week diet trial (i.e.,1 week full-fluid diet and 1 week healthy eating) as well as a food journaling activity. All patients meet one-on-one or via Telehealth with the nurse practitioner for further assessment including a detailed review of their weight history and past weight loss attempts, blood work and a sleep study to identify and treat any sleep disordered breathing, as necessary. If any other medical concerns are identified, patients are consulted to the appropriate specialist (e.g., cardiologist, endocrinologist, respirologist) based on their comorbid condition. An appointment with one of the three bariatric surgeons in the bariatric surgery clinic is arranged to obtain formal surgical consent.

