### Evaluation of health care utilization and costs

The impact of bariatric surgery on the health system will be examined by comparing health care use and costs (e.g., physician visits, hospitalizations, medications and associated costs) 3 years pre‐and 2 years post‐surgery (Table 2). In NL, the Centre for Health Information (NLCHI) maintains a number of key health-related data sources on behalf of the provincial Ministry of Health. These databases comprehensively capture patient-specific health care resource utilization. These include vital statistics (mortality) and validated, high quality, detailed measurement of the following health care resources and costs: inpatient and outpatient encounters, physician billings, diagnostic tests, procedures, and long-term care use. In addition to providing detailed information allowing patient-specific costing of each encounter, inpatient databases record diagnostic and procedural information using the ICD-10-CA and CCI classification systems [62]. Using unique provincial health insurance numbers, the NLCHI will link the bariatric clinical/research data with administrative health services data and provide the research team with a de‐identified database of health services use and costs for data analysis purposes [63, 64].

**Table 2 Tab2:** Short to mid-term health care use and costs in surgical patients

Cost Category	Units of Resources	Newfoundland & Labrador Source Details	Newfoundland & Labrador Costing Source	Time Frame
1. Inpatient encounters	# of hospitalizations (acute care) Length-of-stay (LOS)	Newfoundland and Labrador Centre for Health Information (NLCHI) Clinical Database Management System (CDMS), based on the Discharge Abstract Database (DAD) includes LOS, procedures performed, associated diagnoses, RIW and complexity values	NLCHI/Canadian Institute for Health Information (CIHI) methodology to cost acute care encounters using resource-intensity-weights (RIW) and complexity values	Provided by fiscal year. Referenced to time zero (date of surgery)
2. Outpatient encounters	# encounters # procedures	NLCHI CDMS (based on DAD) includes surgical day care procedures	NLCHI/CIHI methodology to cost surgical day care encounters	Provided by fiscal year. Referenced to time zero
3. Physician Fees (Fee for Service)	# of encounters Provider specialty Service provided	Medical Care Plan (MCP) Physician Claims	MCP Physician Claims	Provided by fiscal year. Referenced to time zero

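### The pre-surgery cost window runs to the date of surgery, so encounters generated by the mandatory work-up count as baseline use rather than as a cost of delivering LSG

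*Protocol article*

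**What the plan says.** Under Secondary outcomes, the protocol article states that direct and indirect costs "will be compared 3 years prior to surgery and 2 years post- surgery in order to determine the economic consequences of bariatric surgery". The section on evaluation of health care utilization and costs gives the same two windows. In its Table 2 the inpatient row is "Referenced to time zero (date of surgery"; the outpatient and fee-for-service physician rows use the same time zero.

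The section on patient selection criteria describes what happens before that date. It says that "patients are required to undergo an extensive pre-operative work-up". Besides the orientation session, diet trial and nurse practitioner assessment, it names "blood work and a sleep study to identify and treat any sleep disordered breathing, as necessary". Where other medical concerns are found, "patients are consulted to the appropriate specialist (e.g., cardiologist, endocrinologist, respirologist) based on their comorbid condition". Finally, "An appointment with one of the three bariatric surgeons in the bariatric surgery clinic is arranged to obtain formal surgical consent".

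The linked provincial databases are said to hold "inpatient and outpatient encounters, physician billings, diagnostic tests, procedures, and long-term care use". The hypothesis under Study objective is "a decrease in direct healthcare and indirect costs compared to pre-surgery costs". Neither the economic sections nor Data analysis excludes work-up encounters, inserts a gap before surgery or ends the baseline at referral.

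**The concern.** Work-up done because surgery is planned is part of the cost of providing LSG. With the boundary at the date of surgery, it enters the baseline instead, with two effects. The comparator is higher than the use the patient would have had without entering the surgical pathway. The cost of the intervention is also too low, which matters for the planned cost-effectiveness analysis.

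The study has no comparison group, so the patient's own pre-surgery period is the only reference for the hypothesised fall in costs. The work-up is required of every patient, so it acts as a systematic shift. Medians and paired tests, as planned under Data analysis, do not remove it, nor does putting the 3-year and 2-year windows on an annual basis.

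**Working it through.** The article gives no utilisation or cost figure, so there is nothing to reproduce. The check has two parts.

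**1. What the text fixes**

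- Boundary between the windows: date of surgery (Table 2).
- Work-up: mandatory and before that boundary (Patient selection criteria).
- Capture: specialist and surgeon consultations fit the physician-claims row of Table 2. Blood work and the sleep study are less clear: the text says the databases hold diagnostic tests, but Table 2 has no row for them, and its outpatient source is described by surgical day care. Nurse practitioner contacts have no clear row.
- Physician contacts that the text implies for every patient: about two, the primary-care referral and one surgeon appointment. Specialist visits are conditional.

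**2. Illustration with no true change in use**

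Let b be background physician encounters per year, the same before and after surgery, and w the work-up encounters in the pre-surgery window. Both are assumptions: b = 6–15 and w = 2–8, where the lower w is the two contacts above.

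- Annualised pre-surgery rate: (3b + w)/3
- Annualised post-surgery rate from background alone: b
- Artefact: w/3 encounters per year, or w/(3b + w) of the pre-surgery rate

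Data collection gives one surgeon visit at 6–8 weeks and six team visits in the first 24 months (1, 3, 6, 12, 18 and 24 months). Counting only the surgeon visit adds 1/2 = 0.5 a year after surgery. Counting all seven adds 7/2 = 3.5 a year.

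| b | w | Pre rate | Artefact per year | % of pre rate | Net, 1 surgeon visit counted | Net, 7 contacts counted |
|---|---|---|---|---|---|---|
| 15 | 2 | 15.67 | 0.67 | 4.3 | 0.17 | −2.83 |
| 8 | 2 | 8.67 | 0.67 | 7.7 | 0.17 | −2.83 |
| 15 | 3 | 16.00 | 1.00 | 6.25 | 0.50 | −2.50 |
| 10 | 5 | 11.67 | 1.67 | 14.3 | 1.17 | −1.83 |
| 6 | 8 | 8.67 | 2.67 | 30.8 | 2.17 | −0.83 |

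A positive net is an apparent saving and a negative net an apparent increase. In the second row, counting the surgeon visit gives 8.67 before against 8.50 after, a difference of about 2 %.

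With f follow-up contacts counted after surgery, the net is w/3 − f/2, which is zero at f = 2w/3. For w = 3 that is 2 contacts; for w = 8 it is 5.3. The sign therefore depends on which contacts are costed.

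If the baseline ends at referral, its rate is b and this artefact is zero. If the referral-to-surgery interval lasts t years, use in it is bt + w. Charging all of it to surgery would move bt of ordinary care to the surgery side; charging only the excess over the pre-referral rate gives (bt + w) − bt = w.

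The illustration annualises both windows. Raw totals would differ by 1 − 2b/3b = 33 % from window length alone, which is a separate matter.

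**The case against.** A reader might infer that the plan is bound to show a spurious saving, and of a definite size. The document supports neither. Every patient also has programme follow-up after surgery, and in the illustration counting all seven contacts turns the result into an apparent increase. The index admission is assigned to neither window and would offset a saving if counted after surgery. Most of what the work-up requires of everyone is not clearly physician-billed, and the frequency of specialist referral is not given. This stands, and it limits what can be said about size and net direction.

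It does not remove the misallocation. Follow-up is a cost of LSG and correctly sits after surgery; work-up is also a cost of LSG but sits in the comparator. A correctly placed cost does not repair a misplaced one.

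Second, some work-up is care for existing disease: the specialist visits follow the comorbid condition, and the sleep study serves treatment as well as clearance. This also stands. It argues against charging the whole interval to surgery, and the change below respects it.

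Third, a condensed article may leave cost allocation to a fuller plan. That would answer mere silence, but here the windows and time zero are stated, and applying them as written puts the work-up in the baseline.

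**Conclusion.** The point holds for this component of the contrast. Ending the baseline at the date of surgery counts work-up encounters as prior use, inflates the comparator and understates the cost of delivering LSG. The direction of this component favours the hypothesis.

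Its size is not derivable from the article. Under the assumed ranges it is roughly 4 % to 31 % of annualised pre-surgery physician encounters before any follow-up is counted, and about 2 % in the case of two work-up contacts set against one surgeon visit with b = 8. These figures concern encounters, not costs, and rest wholly on assumed counts. The net sign of the planned comparison remains open. The change is worth making because this is the study's only evidence on costs, although the outcome is secondary.

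**What to change.** For the linked administrative data:

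- End the baseline window at the date of referral to central intake, taken from the standardized referral form, and compare annualised rates.
- Report the referral-to-surgery interval and the index admission as a separate line.
- In the net economic result, charge to the intervention only identifiable work-up items, or use above the pre-referral rate, plus the index admission.
- Keep the surgery-date cut as a sensitivity analysis.

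The interview-based rows of Table 2 (self-reported physician visits, medications, transfer payments, employment and absenteeism, weight loss interventions, mobility and medical items) cannot be re-anchored this way. Patients are approached only once deemed eligible for surgery, so those rows keep their existing baseline and the report should state the limitation.

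The cost is small for the linked rows: one added date in the linkage file and a new cut of dated encounters, with no new patient contact. The baseline becomes shorter by the wait from referral to surgery unless the extract starts earlier, and the apparent saving will look less favourable.
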